### Eligibility criteria

2.6

Participants will be adults aged >18 years old, able to give explicit informed consent, referred to an intermediary, and that the intermediary facilitates a connection to local physical activities. Inclusion and exclusion criteria are listed in Table 1.

**Table 1 tbl1:** Study inclusion and exclusion criteria.

Inclusion criteria	• Aged ≥18 years • Referred to intermediary service for any reason OR self-referred to intermediary service for any reason • Meets the eligibility criteria of the intermediary service • Intermediary facilitates a connection to local physical activity
Exclusion criteria	• Non-community-dwelling e.g., hospital in-patients, living in residential care facilities • Diagnosis of dementia • Inappropriate for health or social reasons (such as terminal illness, family or other social crisis) • Refused to engage with the intermediary service • Unable to give explicit informed consent

### Sample size

2.7

Convenience sampling will be used, which involves selection of participants based on availability and accessibility [40]. The limitations of non-probability sampling techniques are that it may not create a sample that is representative of the population referred to an intermediary, and that it may introduce selection bias [41]. However, convenience sampling is economical, accessible, and has been used in previous feasibility studies investigating intermediaries [26,27]. Therefore, it was selected for this proposed study. The target sample size will be 30 participants, with approximately 15 participants recruited by SPLW and 15 by LSPO. As this proposed study will have three outcome measures (See Section 2.9 ‘Outcomes’), the sample size has been calculated based on the 10 participants per candidate predictor (variable) rule [42,43]. This rule has been used for multivariable methods of analysis, to reduce the risk of unstable risk estimates and misleading associations that could occur with two few or too many events per variable [44].

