iv To describe the demographic and health characteristics of intervention participants.	The age, gender, marital status, urban/rural, level of education, ethnicity, employment status, self-reported presence/absence of chronic condition, self-reported rating of health, and types of exercise currently undertaken of the study sample	Data collection form items #1-10	**✘**	**✘** (Items #9–10 only)	
v To determine participation in and adherence to local physical activities by intervention participants.	Changes in types of exercise undertaken by participants from Week 0 to Week 12 - including self-directed physical activity and/or local physical activities accessed as a result of the intervention	Data collection form item #10 - *“What types of exercise do you do currently? Please provide a list.”* Intervention participant semi-structured interview item #3 - Includes prompts about what local physical activities were accessed as a result of the intervention, and adherence to the local physical activity	**✘**	**✘** **✘**	
vi To explore the acceptability of the intervention delivered by the intermediary.	Explore intervention content and delivery by the intermediary, the impact of the support provided, and how acceptable the intervention was to the participant.	Intervention participant semi-structured interview items #1–6, 11 Intervention acceptability NRS (Intervention participant semi-structured interview item #10)		**✘** **✘**	
vii To explore suitability, acceptability and completion rates of the measurement tools by intervention participants.	Determine if the outcome measures used in this proposed study captured important information/improvements made by the participant, the rates of completion of each outcome measure, and explore experience of completing the outcome measures.	Intervention participant semi-structured interview items #7-9 # (%) items completed in data collection form items #1–10, SWEMWBS, SEE, IPAQ and intervention participant semi-structured interview items #1-11	**✘**	**✘** **✘**	
viii To assess if change occurs in physical activity and health-related outcomes following participation in the intervention.	Change in IPAQ-SF score from Week 0 to Week 12 Change in SEE score from Week 0 to Week 12 Change in SWEMWBS score from Week 0 to Week 12 Changes in self-rated rating of health from Week 0 to Week 12	IPAQ-SF SEE SWEMWBS Data collection form item #9	**✘** **✘** **✘** **✘**	**✘** **✘** **✘** **✘**	

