### Data analysis

2.11

Quantitative data analysis will be performed using SPSS V28 (IBM, USA) and Microsoft Excel software (Microsoft Corporation, USA). Categorical variables (counts and proportions) and graphical representations e.g., bar charts will be used to present feasibility outcomes. Summary statistics for continuous variables will also be presented as (i) means and standard deviations for normally distributed data, and (ii) median and interquartile ranges for data which was not normally distributed. Within-group differences will be assessed using paired T-tests for normally distributed data and Wilcoxon signed rank tests for data which are not normally distributed.

A qualitative descriptive approach will be taken to the analysis of the exit interviews and free text responses, with the aim of providing a rich, straight description of an experience or an event close to the participant's language [39]. Interviews will be digitally recorded and transcribed verbatim. Transcripts will be analysed using an inductive qualitative content analysis as described by Elo & Kyngäs [55]. Themes will be developed in a four step approach; initialization, construction, rectification and finalization [56]. One researcher [[name]] will analyse all transcripts using NVivo 14 (QSR International, Australia). The qualitative and quantitative data will then be integrated to provide a comprehensive analysis [37,57].

Progression criteria were not developed for this proposed study, as guidance regarding the application and development of progression criteria for non-randomised feasibility trials is limited [58,59]. In addition, progression criteria are generally used to decide whether to progress a feasibility trial to a definitive controlled trial [60]. It is not yet clear whether a controlled or experimental trial will be the most appropriate methodology for the next phase of this research. By examining feasibility and acceptability of the evaluation design in this proposed study, it is anticipated this will inform future research and trial design.

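### Section 2.7 derives the sample size of 30 from a per-predictor regression rule applied to three outcome measures, and no multivariable model is planned, so the stated basis does not support the number

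*Protocol article*

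**What the plan says.** The article's sample size section (2.7) states: "The target sample size will be 30 participants, with approximately 15 participants recruited by SPLW and 15 by LSPO". It gives the reason in one sentence, which opens "As this proposed study will have three outcome measures" and goes on to say that "the sample size has been calculated based on the 10 participants per candidate predictor (variable) rule". The next sentence gives the rule's purpose: "This rule has been used for multivariable methods of analysis, to reduce the risk of unstable risk estimates and misleading associations", with a reference to the number of events per variable.

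Sections 2.9.2 to 2.9.4 describe the three instruments: the IPAQ-SF, the SEE and the SWEMWBS. Table 2 (objective viii) and section 2.9.1 use each as a score whose change from week 0 to week 12 is examined.

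The analysis section (2.11) has two quantitative parts. For feasibility: "Categorical variables (counts and proportions) and graphical representations e.g., bar charts will be used to present feasibility outcomes". For change: "Within-group differences will be assessed using paired T-tests for normally distributed data and Wilcoxon signed rank tests for data which are not normally distributed".

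Section 2.7 also discusses convenience sampling, but that concerns how participants are chosen, not how many.

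**The concern.** A rule of 10 per candidate predictor limits how many explanatory variables a regression can carry for the data available. Its input is a count of predictors. Section 2.7 supplies a count of outcomes instead, and section 2.11 contains no regression, no candidate predictor and no event outcome to which the rule could apply.

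Two things follow. The only reason given for 30 is not a reason for it. The wording also tells readers that the size guards against unstable estimates and misleading associations, when nothing in the planned analysis receives that protection.

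This matters because several objectives of the study are rates: recruitment (i), retention (iii) and completion of the measures (vii). The article sets no progression criteria and expects the results to inform later design. Readers will need to know how precisely those rates are estimated, and the present rationale does not address this.

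**Working it through.** **Step 1. Reproduce the stated figure.** Inputs from section 2.7: 10 participants per variable and 3 outcome measures. 10 × 3 = 30. The arithmetic is right. No alpha, power, effect size, SD, target precision or attrition figure is given in that section, so no other formula can be tested against 30.

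**Step 2. Check the input to the rule.** The rule takes the number of candidate predictors in a multivariable model.
- Role of the three questionnaires (section 2.9, Table 2 objective viii): outcomes, measured at week 0 and week 12.
- Candidate predictors in section 2.11: none.
- Multivariable models in section 2.11: none. The tests are paired and within-group.

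With no predictors, the rule returns no sample size. It neither supports 30 nor speaks against it.

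**Step 3. What 30 provides for a proportion.** Retention (objective iii) has the enrolled participants as its denominator. The article gives no expected retention, so 80% is assumed for illustration. The Wilson 95% interval, with z = 1.96, is

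[p + z²/(2n) ± z√(p(1−p)/n + z²/(4n²))] / (1 + z²/n)

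- Overall, 24/30: the centre is (0.8 + 0.0640)/1.1281 = 0.766 and the half-width is 1.96 × √(0.005333 + 0.001067)/1.1281 = 0.139. The interval is 0.627 to 0.905 (upper limit 0.90495 before rounding), or 63% to 90%.
- One service type, 12/15: the centre is (0.8 + 0.1281)/1.2561 = 0.739 and the half-width is 1.96 × √(0.010667 + 0.004268)/1.2561 = 0.191. The interval is 0.548 to 0.930, or 55% to 93%.
- Other assumed values at n = 30: 21/30 (70%) gives 52% to 83%; 27/30 (90%) gives 74% to 97%.

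These intervals apply to proportions of those enrolled. The recruitment proportions in objective i have the people approached or eligible as denominator, a number the article does not give.

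**Step 4. What it provides for a mean change.** The 95% half-width in units of the SD of the change is t(0.975, m−1)/√m, where m is the number of complete pairs.
- m = 30: 2.045/5.477 = 0.37 SD.
- m = 24 (assumed, 20% without a week-12 assessment): 2.069/4.899 = 0.42 SD.

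The true m is unknown; objective iii is there to estimate it.

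**The case against.** The best defence is that nothing of substance depends on the rationale. This is an uncontrolled pilot with a feasibility aim. A feasibility study needs no power calculation, there are no progression thresholds that depend on precision, and the Discussion already says that the pilot nature limits conclusions about effectiveness. The number also has operational context: section 2.8 has eleven services aiming for up to 3–4 participants each, a ceiling of 33 to 44, which accommodates 30. All of this stands, and it limits the severity. It does not rescue the rationale, because section 2.7 does not cite the recruitment capacity as its basis.

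It could also be said that a statistical analysis plan not shown here may contain a regression. Even so, section 2.7 would still have counted outcomes where the rule needs predictors.

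A reader might be tempted by three stronger readings, none of which the article supports:
- **That 30 is too few.** An inapplicable rule shows nothing about adequacy in either direction.
- **That the rule should have given 40**, because Table 2 also lists "Changes in self-rated rating of health from Week 0 to Week 12". Taking the three outcome measures to mean the three named questionnaires is fair: self-rated health is a single item on the data collection form and is described under demographics and health status. Recounting the inputs of a rule that does not apply settles nothing in any case.
- **That attrition has been wrongly ignored.** The article never promises 30 analysed pairs, and retention is something it sets out to measure.

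**Conclusion.** The point holds, at moderate severity. The only stated basis for the sample size is wrong by the article's own description of the rule: outcomes were counted as predictors, and no planned analysis is of the kind the rule serves. The conclusion rests on sections 2.7, 2.9 and 2.11 alone and needs no outside figure.

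The fault lies in the justification. The article gives no ground for calling 30 unsuitable. The precision figures only describe what 30 would deliver; they depend on the assumed 80% retention and the assumed 24 pairs, and they are not a test that the study fails.

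**What to change.** Rewrite the justification in section 2.7:
- Delete the 10-per-variable rule and the sentence on multivariable methods.
- State that 30, about 15 per service type, is a pragmatic feasibility size and was not chosen to test change.
- Give the precision it yields, labelled as illustrative. For example, if retention were 80%, the Wilson 95% interval would be 63% to 90% overall (24/30) and 55% to 93% within one service type (12/15).
- Say that the number of week-12 pairs is unknown and will be estimated under objective iii, and that the 95% half-width for a mean change would be 0.37 SD with 30 pairs or 0.42 SD with an assumed 24.

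Enrolment should not be increased on account of this point. The cost is one reworded paragraph and a plainer, less formal basis for the number. No measure or planned analysis changes.

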### Recruitment

2.8

Nineteen services (N = 11 social prescribing services and N = 8 local sports partnership services), who had taken part in an earlier study as part of this research project, were contacted to act as gatekeepers for this proposed study. Out of nineteen services, N = 11 agreed to act as gatekeepers. Therefore, participants will be recruited from eleven social prescribing (N = 7 services) and local sports partnership (N = 4 services) services from across Ireland, with the goal to recruit up to 3–4 participants from each service. Recruitment will take place over a six-month period, commencing in September 2023. As many of these services do not have access to administrative support, intermediaries usually make their own appointments and/or meet with individuals directly. Therefore, potential participants will be recruited by social prescribing link workers and local sports partnership community sports development officers, who will act as gatekeepers. Study posters will be sent to each service and can be used at the discretion of the gatekeeper e.g., for display in offices or when introducing the study to their clients or to share through mailing lists. Recruitment strategies will vary slightly depending on the category of intermediary, as detailed below.

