**Methods:**

This will be a mixed methods pilot feasibility study. Participants will be individuals referred or self-referred to an intermediary and connected to local physical activities. Participants will be recruited through two types of intermediary services in Ireland; social prescribing and local sports partnerships. A total of 30 participants will be recruited (15 per service). Baseline demographic information will be taken upon enrolment to the study and three questionnaires will be completed: the International Physical Activity Questionnaire - Short Form, Self-Efficacy for Exercise Scale and Short Warwick Edinburgh Mental Well-being Scale. The questionnaires will be repeated after 12 weeks and in addition semi-structured interviews will be carried out to explore intervention content and delivery, as well as acceptability of the intervention and evaluation design.

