### Outcomes

2.9

Definitions of outcomes, measurement tools, and time points for data collection are summarised in Table 2.

**Table 2 tbl2:** *Data Methods and Schedule of Measures.* Study objectives, descriptions of their associated measures, data measurement tools and the timeframe of data collection. Abbreviations: Short Warwick-Edinburgh Mental Well-being Scale (SWEMWBS), Self-Efficacy for Exercise Scale (SEE), International Physical Activity Questionnaire - Short Form (IPAQ-SF), Numerical Rating Scale (NRS).

Objectives	Measure Definition	Measurement Tool	Data Collection Timeframe		
			Time 0	Time 1 (12 Weeks)	Post-recruitment period
i To determine the rate of recruitment and enrolment to the proposed study of individuals who undergo an intervention delivered by an intermediary, which includes participation in local physical activities (intervention participants).	How many people are approached/receive information about the study from the gatekeeper - # (%) of total clients referred to an intermediary who will be connected to local physical activities i.e., eligible people - # (%) of eligible people who receive study information How many eligible people take part in the study - # (%) eligible people who receive study information who take part in the study	Gatekeeper recruitment log Gatekeeper recruitment log	Ongoing throughout recruitment period Ongoing throughout recruitment period		
ii To examine the suitability and acceptability of recruitment methods to the proposed study.	How long it takes to recruit 3–4 people from each service/gatekeeper - length of recruitment period per service (days) Reasons given for not taking part - frequency count of reasons given for not taking part in research Explore gatekeepers' perceptions of how open clients were to take part in the research, their experience of recruitment and the acceptability of the recruitment methods.	Gatekeeper recruitment log Gatekeeper recruitment log Gatekeeper semi-structured interview items #1-8	Ongoing throughout recruitment period Ongoing throughout recruitment period		**✘**
iii To determine retention to the proposed study.	How many people return for a follow-up assessment with the research team	# (%) of participants who return for 12-week follow-up assessment		**✘**	

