#### Gatekeeper recruitment logs

2.9.7

Gatekeepers will be asked to keep a record of how many clients they had contact with during the recruitment period, how many people were approached about the study, and the reasons for refusal to take part in the study. This record will be kept until 3–4 participants have been recruited from each participating service. For participants recruited to the study, gatekeepers will also be asked to keep a record of their contacts with this person (date, length of each contact and mode of contact). This will help to verify the data collected from participants in their interview.

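### The per-service endpoint of 3–4 recruits does not fit about 15 social prescribing participants over seven services, and it leaves slow services without a recruitment time

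*Protocol article*

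**What the plan says.** Section 2.7 of the protocol article sets the target: "The target sample size will be 30 participants, with approximately 15 participants recruited by SPLW and 15 by LSPO". Section 2.8 names the recruiting services, "social prescribing (N = 7 services) and local sports partnership (N = 4 services", eleven in all, gives a recruitment period of six months, and states the aim for each service: "with the goal to recruit up to 3–4 participants from each service".

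The same range then appears in two other roles. In Table 2, a measure for objective ii is "How long it takes to recruit 3–4 people from each service/gatekeeper", recorded as the length of the recruitment period per service in days. Section 2.9.7 says of the gatekeeper's log: "This record will be kept until 3–4 participants have been recruited from each participating service". That log is also the source for the recruitment and enrolment percentages of objective i.

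The article does not say that recruitment closes at 15 per service type or at 30 in total. Nor does it say how a service that never reaches 3–4 is recorded.

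**The concern.** A per-service figure that is only a ceiling can sit comfortably above the average needed. Once it becomes an event that every service is timed to, and the signal to stop the log, it has to be attainable within the overall target and the recruitment window. For the SPLW services it is not, if the stated split is followed.

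There are two further difficulties. Because 3–4 is a range, one service's clock may stop at the third recruit and another's at the fourth, so the durations are not comparable. And a service still short of the quota after six months has no time to quota at all. If such services drop out of the summary, only the faster recruiters remain and recruitment looks quicker than it was. Recruitment rate and method are core objectives here, and the results are meant to inform the design of later research.

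**Working it through.** **Inputs.** Target 30, about 15 + 15 (section 2.7). Services 7 SPLW + 4 LSPO = 11 (section 2.8). Per-service figure 3–4 (section 2.8, Table 2, section 2.9.7). Window six months (section 2.8).

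**The plan's own figure.** Section 2.7 bases the sample size on 10 participants per variable with three outcome measures: 10 × 3 = 30. This reproduces.

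**Step 1: services × quota against the target.**

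| | Services | At 3 each | At 4 each | Target | Average needed |
|---|---|---|---|---|---|
| SPLW | 7 | 21 | 28 | 15 | 15/7 = 2.14 |
| LSPO | 4 | 12 | 16 | 15 | 15/4 = 3.75 |
| All | 11 | 33 | 44 | 30 | 30/11 = 2.73 |

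The LSPO range brackets its target. The SPLW range does not: even 21 is 40% above 15 (21/15 = 1.40), more than an approximate target would normally cover.

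**Step 2: the most services that can reach the endpoint if the split is kept.** This is the whole part of target/quota, limited to the number of services.

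- SPLW, quota 3: 15/3 = 5, so at least 7 − 5 = 2 miss.
- SPLW, quota 4: 15/4 = 3.75, so at most 3 reach it and at least 7 − 3 = 4 miss.
- LSPO, quota 3: all 4 can reach it. Quota 4: at most 3 can, so at least 1 misses.

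Over all eleven services, at least 2 miss a quota of three and at least 5 miss a quota of four. If only the total of 30 binds, 30/3 = 10 services could reach three and 7 could reach four (30/4 = 7.5).

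**Step 3: neither end of the range suits both service types.** With a ceiling of 3, LSPO tops out at 12. With a ceiling of 4, LSPO reaches 15 only as 4 + 4 + 4 + 3, while the SPLW endpoint moves further out of reach.

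**Step 4: the six-month window.** This step needs no stop at 15. It assumes, for illustration, that every service recruits as a Poisson process at the planned average, 30/11 = 2.73 per six months (30/66 = 0.4545 per month).

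- P(at least 3) = 0.513 and P(at least 4) = 0.292, so about 49% of services do not reach three and 71% do not reach four.
- Mean time to the third recruit over all services: 3/0.4545 = 6.6 months, about 201 days.
- Mean time among services that reach it within six months: 6.6 × P(at least 4)/P(at least 3) = 6.6 × 0.292/0.513 = 3.76 months, about 114 days.

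At the SPLW pace (2.14 per service), 36% reach three and 17% reach four.

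**Sensitivity.** The gap depends on the assumed pace. A simulation of the SPLW services at 4 recruits per service per 182 days, with no stop at 15, gives a median time to the third recruit of 101 days among services that reach it, against a true 122. With recruitment stopped at 15, the figures are 75 against 122. The direction is the same in both cases.

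**The case against.** The strongest reply is that section 2.8 gives a ceiling and section 2.7 an approximate split. Eleven services allowed up to 3–4 each have room for 33–44, which is compatible with 30 and leaves slack for services that recruit poorly. That is right. A reader might infer that section 2.8 contradicts the target of 30, and the documents do not support this. The conflict arises only where Table 2 and section 2.9.7 turn the ceiling into an endpoint for every service. The LSPO half is consistent as it stands.

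A reader might also infer that many services cannot reach the endpoint. No closure at 15 per type is stated, so the forced shortfall is conditional on keeping the split. Even then it is 2 of 11 at a quota of three, rising to 5 of 11 only at four.

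Thirdly, a reader might conclude that the measure is biased short. That follows only if services that miss the quota are dropped, or if their closing day is read as the time to quota. The article states neither, and Table 2's length of recruitment period can be recorded for any service. The handling may be set out in a fuller protocol or analysis plan. If unfinished services are kept as censored, the bias need not arise.

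Finally, one might argue that stopping the log at the third recruit inflates uptake. With a true uptake of 20%, the average of per-service percentages would be about 26%, but the article does not specify that average. The pooled figure, the more natural reading of Table 2, is about 20.5%, a negligible difference.

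It is also fair to say that no decision rule hangs on this measure. The study has no progression criteria, and objective ii also draws on reasons for refusal and gatekeeper interviews. What survives is the SPLW misfit, the two-valued endpoint, and the lack of a usable time for slow services.

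**Conclusion.** The point holds in a limited form. As an endpoint for each service, 3–4 recruits does not fit about 15 SPLW participants over seven services (21–28 implied). If the 15/15 split is kept, at least 2 of the 7 miss three and at least 4 miss four; these counts are plain arithmetic from the article's own figures. The range is also two different stopping events, and that needs no assumption.

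The consequence for estimated recruitment speed is conditional. About half the services missing three, and 114 against 201 days, rest on equal Poisson rates at the planned average and on a summary confined to services that reached the quota. These figures show what could happen if the handling is left open; they do not describe a stated analysis. The defect does not affect the target of 30 or the LSPO half. It is worth correcting because the correction is cheap and the measure serves a core feasibility objective.

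**What to change.** Reconcile section 2.8, section 2.9.7 and Table 2 as follows.

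1. State guides by service type that add up to the target: about 2–3 per SPLW service (15/7 = 2.14) and about 4 per LSPO service (15/4 = 3.75). Allow open services to exceed them where another under-recruits.
2. Keep every gatekeeper log open to one fixed date, either the end of the six months or study closure, whatever number has been recruited.
3. Report participants recruited per service-month as the measure of recruitment speed. Every service then contributes a value, including one that recruits nobody.
4. If time to quota is kept, define it by a single number, such as the third recruit, and report services that do not get there as censored or simply as not reached. With at most eleven services, a count of those not reached may be enough.

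The cost is a few sentences of wording, and some gatekeepers keep the log for longer.
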